### Data management

#### Patient documentation

Study participants will be uniquely organized and documented in all clinics through an automated documentation template. All aftercare agents will be briefed on the template before recruitment.

The included study participants will receive an identification number (ID) to pseudomize their personal data. The first number serves the classification of the intervention and control groups. The subsequent numbering corresponds to the number of addressed participants. Personal data will be only documented in an independent Excel file; by the ID, an appropriate linkage occurs. The data will not be sent to the ISE until the personal contents are deleted. This collection only serves the standardized documentation in the clinics. The data from the questionnaire will be collected and kept apart from the ISE.

### Data entry and control

In the context of the quantitative part of the study, (A) data from the written survey will be captured by the acquisition software TeleForm®. The answers from the questionnaires will be scanned by this software and finally transmitted directly into SPSS 22.0. The unrecorded answers will be completed by a student assistant under the guidance of a scientific employee.

### Data monitoring

This study does not contain drugs; ReNaApp investigates the health benefits of an aftercare programme fitted to the individual abilities of the patients. Therefore, no harmful or undesirable events are to be expected.

Our study is accompanied and advised by a data and safety monitoring committee. An interim analysis is not planned.

### Case number calculation/sample size

According to the time and primary outcomes, we expect that both groups (control and intervention groups) will similarly improve until the end of rehab. In the following period, the effects in the CG will approach the starting level before rehab, while the positive changes in the IG will stabilize and even increase slightly. We assume that the intervention group will return to work with higher likelihood and earlier than the CG.

Regarding the needed sample size, the primary outcome *restriction in participation* (IMET [42]) will be involved. For this purpose, we have results from our own studies about the influence of “Neues Credo”. To determine the effect of data on the Quality Community for Medical Rehabilitation (QGmR, indication oncology) [52], the controlled trial of “Neues Credo” [14] and the feasibility study of “Neues Credo” [15] were taken into account.

The QGmR data from oncological patients who followed a standard rehab and standard aftercare did not show an effect (ES = 0.05) on participation after a four-month follow-up. The IG participation in the controlled trial of “Neues Credo” showed an effect intensity of ES = 0.42 in a 12-month follow-up, and the control group showed an effect intensity of ES = 0.06. Psychosomatic rehabilitants reached an effect intensity of ES = 0.53 for participation after a four-month follow-up in the feasibility study of “Neues Credo”.

Calculating the sample size, we assume clinically relevant and positive effects (pre-catamnesis-ES = 0.40) in *social and work-related participation* (IMET [42]) in the IG after a 12-month follow-up. Compared to the intervention group, the control group does not show any effects to the point of catamnesis. The other two primary outcomes are expected to show comparable effect intensity [79–81]. To demonstrate differences between the IG and CG after a 12-month follow-up, we require a magnitude of ES = 0.40 by double-sided testing with α = 1.6% (Bonferroni correction for three primary outcomes) with a power of 80%. That is why the intervention and control groups need a net sample size of *n* = 235 for each. We expect a dropout rate of 30% from patients with oncological rehab (according to experiences in QGmR oncology). To analyse each group of n = 235 patients, we must initially recruit 336 participants for the study; i.e., every rehab clinic has to recruit 112 participants (56 participants in each group).

With propensity score matching (PSM), it is possible that not all participants will have a match despite the use of a caliper. The equalization of these matching failures justifies a 10% higher sample size; thus, 740 patients must be recruited (*n* = 370 for IG and CG). Taking into account that 30% of those asked will refuse to participate in the study, 528 patients of each group must be addressed to participate in the study. In summary, each clinic will address *n* = 176 patients, 88 patients in each group. Because the study does not examine differences between the clinics, the rehabilitants of each clinic will be considered as one group at the end of recruitment.

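### The net sample size of 235 per group does not follow from the stated ES of 0.40, two-sided alpha of 1.6% and 80% power, which need about 134 per group

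*Protocol article*

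**What the plan says.** All inputs are in the protocol article, Methods, Case number calculation/sample size. The calculation rests on one of the three primary outcomes, restriction in participation (IMET).

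- **Intervention group:** "we assume clinically relevant and positive effects (pre-catamnesis-ES = 0.40") at the 12-month follow-up.
- **Control group:** "the control group does not show any effects to the point of catamnesis".
- **Target:** "To demonstrate differences between the IG and CG after a 12-month follow-up, we require a magnitude of ES = 0.40 by double-sided testing".
- **Error rates:** "by double-sided testing with α = 1.6% (Bonferroni correction for three primary outcomes) with a power of 80" percent.
- **Result, given as the consequence of the above:** "the intervention and control groups need a net sample size of" 235 each.

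The section then adds 30% for dropout, which gives 336, and 10% for patients who find no match in the propensity score matching. From this, "thus, 740 patients must be recruited", 370 per group. Allowing for 30% refusals, 528 are to be approached per group.

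The evidence cited for the effect includes a controlled trial of the same aftercare concept. There the intervention group had an effect of 0.42 at 12 months, and "the control group showed an effect intensity of ES = 0.06".

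**The concern.** The section prints a complete calculation: effect, sidedness, alpha, power and result. A reader who repeats it does not get the printed result, and the gap is far too large to be rounding.

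What is at stake is the meaning of the planned size, not its adequacy for the stated effect. If 0.40 is the target, the plan recruits many more patients than its own justification asks for. If the target was about 0.30, the section misstates the effect that the trial is designed to detect.

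The two readings lead to different decisions if recruitment or follow-up falls short. With, say, 180 analysed per group (an illustrative figure), power at two-sided alpha 1.6% would be about 91% for an effect of 0.40 but about 66% for 0.30. The article as written does not tell the sponsor which of these applies.

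**Working it through.** **Inputs, all from the sample size section:** between-group ES 0.40; two-sided alpha 0.016 (0.05/3 = 0.0167, rounded down); power 0.80; equal groups; stated net size 235 per group.

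**1. Attempt to reproduce 235.** For two independent groups and a standardised difference ES,

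n per group = 2 (z₁₋α/₂ + z₁₋β)² / ES²

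with z₀.₉₉₂ = 2.409 and z₀.₈₀ = 0.842. The squared sum is 3.2505² = 10.566.

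- ES 0.40: 2 × 10.566 / 0.16 = 132.1, so 133. The t-test gives 133.5, so 134.
- With alpha 0.05/3 instead of 0.016, the t-test gives 132.3, so 133.

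The stated 235 is not reproduced: 235 / 134 = 1.75.

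**2. What 235 per group delivers** (noncentral t, two-sided alpha 0.016).

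| Between-group ES | Power at 235 per group | n per group for 80% power, normal / t-test |
|---|---|---|
| 0.40 | 97.2% | 133 / 134 |
| 0.36 (0.42 − 0.06) | 93.1% | 164 / 165 |
| 0.30 | 79.8% | 235 / 237 |

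The effect detectable with 80% power is 3.2505 / √(235/2) = 3.2505 / 10.840 = 0.300 (0.301 by the t-test).

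An effect of 0.30 gives 235 by the normal formula at alpha 0.016 (2 × 10.566 / 0.09 = 234.8) and by the t-test at alpha 0.05/3 (234.1). By the t-test at alpha 0.016 it gives 237. So 235 fits an effect of about 0.30, though not under every convention.

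**3. Could a stated allowance explain the gap?** No. Dropout and the matching allowance are applied after 235:

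- 235 / 0.7 = 335.7, so 336
- 336 × 1.1 = 369.6, so 370 per group and 740 in total
- 370 / 0.7 = 528.6, given as 528

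The same steps from 134 give 134 / 0.7 = 191.4, so 192. With the 10% allowance this becomes 134 / 0.7 × 1.1 = 210.6, so 211 per group and 422 in total.

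**4. Could another method explain it?** With ES 0.40 and the other inputs held as stated unless noted, n per group is:

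- one-sided test: 112
- rank test with efficiency 0.955 or 0.864: 140 or 155
- alpha halved to 0.008: 153
- alpha divided by three again: 165
- joint 80% power over three outcomes, taken as independent: 188
- 95% power: 206

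None reaches 235. If 235 is read as the total, power at 0.40 is only 74%.

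Two unstated assumptions would bridge the gap:

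- *Change scores, with ES scaled to the baseline SD.* The variance factor is 2(1 − ρ), so 132.07 × 2(1 − ρ) = 235 gives ρ = 0.11. A correlation of 0.1 gives 238, and 0.5 gives 133.
- *A design effect* of 235 / 132.07 = 1.78.

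The section states neither. It says that the clinics will be treated as one group.

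**The case against.** The strongest reply is that the discrepancy is harmless. At the stated effect and alpha, 235 per group exceeds the required 80% power by a wide margin. No analysis changes, no conclusion is biased, and what a null result excludes will be read from the confidence interval. All of that stands. It limits the consequence, but it does not make the printed calculation correct.

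A second reply is that the planned repeated-measures analysis would allow a different formula. That is possible in principle, but it reaches 235 only with a pre-post correlation near 0.11, and none is given.

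Third, the calculation concerns one of three primary outcomes. Return to work is analysed by discrete-time survival models and could need a different number. This also stands, so 422 is what the printed IMET inputs imply, not a proposal for the trial's size. It does not explain 235, which the section derives from the IMET effect.

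Three stronger readings are tempting, and the document does not support them.

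- *That 0.30 was the effect actually used.* The value appears nowhere in the article. Other altered inputs also come close: ES 0.30 with alpha 5% and 90% power gives 234 by the normal formula, and ES 0.34 with alpha 1.6% and 90% power gives 236. The origin of 235 cannot be established.
- *That a within-group effect was wrongly used as a between-group one.* The section openly assumes no control effect, and under that assumption the two coincide. Setting observed control effects of 0.05 and 0.06 to zero is a declared planning choice. At 235 per group, 0.36 still has about 93% power.
- *That the cited evidence supports only a range such as 0.34 to 0.36.* The one controlled comparison gives 0.36. The figure 0.34 would subtract an observed control effect from an assumed intervention effect. The section also cites 0.53 from a feasibility study, which is weaker evidence (four months, psychosomatic patients, no control result given) but was taken into account.

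**Conclusion.** The point holds as an internal contradiction. An effect of 0.40, two-sided alpha 1.6% and 80% power require 133 to 134 per group, and the article states 235. At 235 the power for 0.40 is about 97%, and the effect detectable with 80% power is about 0.30. The recruitment figures inherit the discrepancy, including the 740 in the abstract.

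The error is conservative for power at the stated effect. What is wrong is the planning statement: effect, power and size cannot all be right as printed.

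This rests on a comparison of two equal, independent groups on a standardised difference, with no variance inflation, which is how the section presents it. A stated pre-post correlation or design effect could change the arithmetic, and the article gives none.

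**What to change.** Keep 235 net per group and 740 recruited, and correct the sentence so that effect, power and size agree at two-sided alpha 1.6%. Either of these would do:

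- 235 per group gives about 97% power for a between-group ES of 0.40; or
- 235 per group gives 80% power for a between-group ES of about 0.30.

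The sponsor should choose the version that reflects the effect the trial was meant to detect. The power of about 93% for 0.36, the difference in the cited controlled trial, may be added for reference. If a variance inflation or a pre-post correlation was used to arrive at 235, state its value and the formula instead.

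The cost is a wording change in the sample size section. It needs no extra patients and no change to the analysis.

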### Immediate expected results of the project

The use of ReNaApp for 12 months leads to clinically relevant and positive effects (pre-post-ES > 0.40) in different primary outcomes after rehab. In addition to a significant increase in social and work-related participation in the IG, breast cancer patients in the IG return faster and more often to work than patients following the standard aftercare programme. This is accompanied by lower indirect costs in the IG. Furthermore, the quality of life increases.

The extent of restriction in social and work-related participation and the quality of life of the control group are comparable to the conditions of the intervention group at the beginning of rehab. Additionally, the participants in the control group returned to work less often and later than participants in the intervention group.

Compared to the CG participants, IG participants using ReNaApp show significant positive effects in all secondary outcomes 1 year after rehab. This includes less physical, psychological and occupational stress as well as a better prognosis of employment and work ability.

Last, the intervention group shows differences compared to the control group regarding a significantly stronger extent of physical activity 1 year after rehab. Unlike the patients in the control group, the breast cancer patients in the intervention group more often engage in self-engaged fitness training or sports programmes though the ReNaApp; they practice significantly more endurance sports.

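### Single-step Bonferroni at 1.6% is the only rule named for the three primary outcomes; Holm's step-down test would be at least as powerful at 5% family-wise error without extra patients

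*Protocol article*

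**What the plan says.** The protocol article names three primary outcomes: participation (IMET), breast cancer-specific quality of life, and return to work. Under Case number calculation/sample size it sets "double-sided testing with α = 1.6% (Bonferroni correction for three primary outcomes) with a power of 80" per cent, with a required effect of 0.40 ("we require a magnitude of ES = 0.40 by double-sided testing") and a net 235 patients per group. It assumes no change in the control group ("the control group does not show any effects to the point of catamnesis"). For the remaining two outcomes it says: "The other two primary outcomes are expected to show comparable effect intensity". The section on immediate expected results repeats the expectation of benefit on several outcomes: the app "leads to clinically relevant and positive effects (pre-post-ES > 0.40) in different primary outcomes after rehab".

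The Statistical methods section lists repeated-measures analysis of variance, contingency tables and discrete-time survival models. It names no multiplicity procedure and excludes none. The Data monitoring section plans no interim analysis, so the three outcomes are the only source of multiplicity that the sizing has to cover.

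**The concern.** Under single-step Bonferroni each outcome is judged at 1.6% whatever the other two show. Holm tests the smallest p-value at 5%/3, the next at 2.5% and the last at 5%, stopping at the first failure. Its first step is no stricter than 1.6% and its later steps are more lenient, so it can never reject less. It needs no assumption about correlation.

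Holm gains most when several effects are real, which is what this protocol expects. At stake is a missed true effect on a second or third primary outcome that the same data could have shown at the same 5% family-wise error.

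**Working it through.** **Inputs.** Two-sided alpha 1.6% per outcome, power 80%, ES 0.40, 235 per group, comparable effects on all three outcomes: all from the sample-size section. The correlation between the outcomes is not given; I assume a range of 0 to 0.8.

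**1. Alpha spent.** 3 × 1.6% = 4.8%; 5%/3 = 1.67%. The rule stays within 5%, and rounding down leaves 0.2 points unused.

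**2. The plan's own sample size.** n per group = 2(z₀.₉₉₂ + z₀.₈₀)²/ES².
- ES 0.40: 2(2.409 + 0.842)²/0.16 = 132.1, so 133, not 235.
- ES 0.30: 2(2.409 + 0.842)²/0.09 = 234.8, so 235.

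The stated 235 is therefore not reproduced from ES 0.40, but it is from ES 0.30, a value the document does not give. With 235 per group, the expected test statistic is ES × √(235/2), which is 4.336 at ES 0.40 and 3.252 at ES 0.30. Power at 1.6% is then 97.3% and 80.0% respectively. Because the stated power conflicts with the stated n and ES, the gain has to be shown for both.

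**3. Hand check, independent outcomes, 80% power.** With the expected statistic at 3.252, power is 0.8045 at 5%/3, 0.8439 at 2.5% and 0.9018 at 5%. Put q₁ = 0.8045, q₂ = 0.8439 − 0.8045 = 0.0393 (from unrounded values) and q₃ = 0.9018 − 0.8439 = 0.0579. Holm rejects all three with probability

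q₁³ + 3q₁²q₂ + 3q₁²q₃ + 3q₁q₂² + 6q₁q₂q₃ = 0.5208 + 0.0764 + 0.1125 + 0.0037 + 0.0110 = 0.724.

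Bonferroni at 1.6% gives 0.8004³ = 0.513.

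**4. Simulation.** Trivariate normal test statistics with common correlation 0, 0.3, 0.5 and 0.8; Bonferroni at 1.6% against Holm at 5%/3, 2.5% and 5%. Ranges run over the correlations.

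| Scenario | Bonferroni | Holm |
|---|---|---|
| 80% power, three real effects: per outcome | 80% | 86–88% |
| 80% power, three real effects: all three shown | 51–69% | 72–81% |
| 80% power, two real effects: per real outcome | 80% | 83–84% |
| 80% power, one real effect: that outcome | 80% | 80.5% |
| n = 235 and ES 0.40, three real effects: per outcome | 97.3% | 98.6–99.1% |
| n = 235 and ES 0.40, three real effects: all three shown | 92–95% | 97–98% |

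The chance of at least one success rises by at most 0.4 points. That difference comes only from using 5%/3 instead of 1.6%; at the same total alpha it is identical. Holm's family-wise error stayed below 5% in every configuration with one, two or three null effects.

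**The case against.** The strongest reply is that nothing here is wrong. Bonferroni controls the error. The 1.6% appears only in the sample-size section, and sizing at about alpha/3 is fully compatible with a Holm analysis, because alpha/3 is Holm's first step. A reader might infer that the protocol locks the final analysis into single-step testing. The text does not go that far: the analysis section is silent, and an analysis plan that is not shown may settle it. This stands. The point is only that the one rule on record is the less efficient one.

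A reader might also take the rise from 80% to 88% as the gain at the plan's own inputs, or conclude that power rises materially on every outcome. Neither is supported. The 80% figure conflicts with the stated n and ES, which give about 97% and leave little to gain. An outcome gains appreciably only if another outcome also has a real effect. The document does not define success as winning on all three, so the all-three figures illustrate the gain but do not describe a criterion of the trial.

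Finally, Holm orders one p-value per outcome, whereas quality of life is measured with two questionnaires with several subscales, and return to work covers both whether and when. The simulation treats the outcomes as three equally powered normal statistics, so its figures are approximate. This also stands, and the fix has to cover it. What does not stand is that the choice is mere taste: at family-wise 5% Holm is never worse than the stated rule in what it rejects.

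**Conclusion.** The concern holds as an efficiency point. If all three effects are real, naming Holm instead of single-step Bonferroni would add about 6–8 points of power per outcome at the stated 80% power, but only about 1–2 points if n = 235 and ES 0.40 both hold. At 80% power it would add about 3–4 points with two real effects and about 0.5 points with one. The chance of at least one success hardly moves. These sizes rest on the assumed correlation range of 0 to 0.8 and on comparable effects across outcomes, as the protocol expects. It would be wrong to read this as a failure of error control or as a flaw that endangers the trial's conclusions.

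**What to change.** State in the Statistical methods section that the three primary outcomes, each represented by one pre-specified p-value, are tested with the Holm step-down procedure at family-wise two-sided 5% (steps 5%/3, 2.5% and 5%). Name the subscale or score that represents quality of life and the single test that represents return to work. Keep 5%/3 as the level for sizing, in place of the rounded 1.6%.

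The change should be made before the data are analysed. It needs no extra patients, data or correlation assumptions. The one downside is that simultaneous confidence intervals matching Holm are less simple; Bonferroni intervals can still be reported alongside the Holm decisions.

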### Study design

The study is organized as a mixed-methods study [41] with different methodological components (sections A-D). The leader of the study is the Institute for Social Medicine and Epidemiology of the University of Lübeck. The recruitment takes place in five different rehabilitation clinics in Germany (AMEOS Reha Klinikum Ratzeburg, Klinik Graal-Müritz, Strandklinik Ostseebad Boltenhagen, Asklepios Klinik Am Kurpark Bad Schwartau, Sonneneck Nordsee-Fachklinik Wyk auf Föhr). The designated aftercare agents of each clinic are responsible for the screening of eligible patients within the first days of their rehabilitation. If applicable, the agents address the patients personally and give them the information sheets and the declaration of consent.

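### The per-clinic recruitment and contact figures do not fit the five clinics named; worked to as quotas, they would yield about 616 participants, not 740

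*Protocol article*

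**What the plan says.** Under Study design, the protocol article states: "The recruitment takes place in five different rehabilitation clinics in Germany". It lists all five by name. The number five recurs in the abstract's Methods, in Eligibility criteria, in part B on qualitative measures and in the section on transferability. No sixth clinic appears anywhere.

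Case number calculation/sample size builds the target in steps:

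- Dropout: "We expect a dropout rate of 30% from patients with oncological rehab", and so "To analyse each group of n = 235 patients, we must initially recruit 336 participants for the study".
- First per-clinic figure: "every rehab clinic has to recruit 112 participants (56 participants in each group").
- Matching: "The equalization of these matching failures justifies a 10% higher sample size", from which "740 patients must be recruited", 370 per group.
- Refusal, also 30%: "528 patients of each group must be addressed to participate in the study".
- Second per-clinic figure: "176 patients, 88 patients in each group".

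Part A, on quantitative measures, describes the sequential design. The control group is filled first, up to its target number of cases. The clinics are then trained in the new programme, and later arrivals form the intervention group.

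**The concern.** The study-level totals and the per-clinic figures should be the same requirement expressed at two levels. They are not, because five clinics that each meet their figure fall short of the total.

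The per-clinic figures are the only site-level targets in the article, so they are what a clinic would naturally plan to. The two groups cannot be recruited at the same time, so a control shortfall noticed only after the clinics have changed their procedures would be hard to make good. The article does not say which figure prevails if the two disagree.

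**Working it through.** **Inputs, all from Case number calculation/sample size except the clinic count (Study design).** Clinics 5; net size 235 per group; dropout 30%; matching allowance 10%; refusal 30%; per clinic 112 recruited (56 per group) and 176 contacted (88 per group).

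**Step 1. Reproduce the study-level totals.**

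- 235 / 0.70 = 335.7, so 336. This must be per group, although the sentence says it is for the study: 235 are needed in each group, and the later 370 per group follows from it. Both groups together: 672.
- 336 × 1.10 = 369.6, so 370 per group and 740 in total.
- 370 / 0.70 = 528.6; the article gives 528 per group, 1,056 in total.

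This chain is sound apart from the trivial rounding down to 528.

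**Step 2. Check the per-clinic figures against five clinics.**

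| Quantity | Per clinic | Five clinics give | Article requires |
|---|---|---|---|
| Recruited per group, before matching allowance | 56 | 280 | 336 |
| Recruited in total, before matching allowance | 112 | 560 | 672 |
| Contacted per group | 88 | 440 | 528 |
| Contacted in total | 176 | 880 | 1,056 |

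Each figure is one sixth short. Rounding cannot explain it: 336 / 5 = 67.2 and 528 / 5 = 105.6.

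The two per-clinic figures do agree with each other: 112 × 1.10 = 123.2 and 176 × 0.70 = 123.2. The fault therefore lies in the division by clinic and nowhere else in the chain.

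**Step 3. What divisor fits?** 6 × 56 = 336 and 6 × 88 = 528, both exact, and 6 × 176 × 0.70 = 739.2, which matches 740. Dividing the per-group totals by three and then halving gives the same figures (336 / 3 = 112, half is 56; 528 / 3 = 176, half is 88). The article states no divisor.

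**Step 4. What five clinics deliver if they stop at 176 contacted.**

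- Recruited: 880 × 0.70 = 616, or 308 per group.
- Shortfall: 740 − 616 = 124; 124 / 740 = 16.8%.
- After dropout: 308 × 0.70 = 215.6 per group.
- After the matching allowance as well: 215.6 / 1.10 = 196 per group.

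Both are below 235. The recruitment figure of 112 gives 560, but it precedes the matching allowance, so its comparator is 672 and not 740.

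**Step 5. Nominal power at the stated assumptions** (effect size 0.40, two-sided alpha 1.6%, normal approximation). Power = Φ(0.40 × √(n/2) − 2.409), where 2.409 is the normal quantile at 0.992.

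- n = 196: Φ(3.960 − 2.409) = Φ(1.551), about 94%.
- n = 215.6: Φ(4.153 − 2.409) = Φ(1.744), about 96%.

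**The case against.** The strongest reply is that the per-clinic figures bind nobody. Part A ends control recruitment when the target number of cases is reached, and that number is stated as 370 per group. The article also pools the clinics for analysis. Nothing describes 88 or 176 as a cap. On this view they are planning averages, and the practical effect is misjudged workload and recruitment time. Most of this stands. A reader might infer that the quotas decide when the control phase closes; the article does not say so, and a sponsor tracking the 370 centrally would notice the gap. What remains is that the article gives two incompatible targets.

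A second reply concerns power. A reader might infer that the trial would be underpowered. At an effect size of 0.30, the value that reproduces 235 per group, 196 per group would give about 71%. But the protocol never states 0.30. It states 0.40, at which 133 per group would already give 80% power. The mismatch between 235 and 0.40 is a separate matter and cannot supply the harm here. This reply stands in full.

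Third, the 196 assumes that matching is used and loses the full allowance. The Limitations section offers covariate adjustment as an alternative; under that, about 216 per group remain. This also stands, though 216 is still below 235.

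Finally, it is tempting to say that the figures were divided over six clinics. The arithmetic is consistent with that, but three with halving fits equally well, so the cause cannot be stated as fact.

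**Conclusion.** The inconsistency is real and exact: the per-clinic figures are one sixth too low for five clinics, at 280 against 336 recruited per group before the matching allowance, and 440 against 528 contacted per group.

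The consequence is conditional. If clinics work to the quotas, and the stated refusal and dropout rates hold, the trial recruits about 616 and ends with about 216 per group, or 196 with full matching loss. It then misses its own net requirement of 235. If recruitment continues to 370 per group, as the sequential design implies, there is no shortfall, only an understated workload for each clinic. Under the stated effect size and alpha, no loss of power below the planned 80% is shown in either case. The conclusion that the figures disagree depends on neither the effect size nor the cause of the error.

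**What to change.** Restate the per-clinic figures for five clinics and keep the total of 740:

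- Recruited: 370 / 5 = 74 per group, 148 per clinic. If a figure before the matching allowance is still wanted, 336 / 5 = 67.2, so 68 per group in place of 56.
- Contacted: 528.6 / 5 = 105.7, so 106 per group, 212 per clinic. Check: 5 × 212 × 0.70 = 742.

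If the quotas are to be kept instead, state the expected total as about 616 and the net group size it gives (about 216, or about 196 after full matching loss).

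In either case, add a sentence saying that the 370 per group, or its replacement, determines when each phase closes, and word the 336 as a per-group number. The cost of the first option is four corrected figures and a notice to the clinics, ideally before control recruitment ends. The trial does not grow, because 740 is already the target.
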